van der Vliet et al [19] advises additional research in nontechnical skills to be performed in different surgical approaches (open, laparoscopic, and robot assisted). Moreover, the use of multiple trained observers is advised for assessing audiovisual recordings of the surgical environment to identify and quantify possible interobserver reliability. The group of Gjeraa et al [18] advises systematic identification of nontechnical skills in minimally invasive surgery in order to develop effective, evidence-based team training programmes for minimally invasive surgeries.

The present study aims to perform a structured evaluation of nontechnical skills in both open and robot-assisted complex surgery, to investigate the manner in which the introduction of a surgical robot influences both nontechnical skills and surgical outcomes during the 1st year of robot-assisted radical cystectomy compared with open radical cystectomy.

In addition, analysis of technical skills in robot-assisted radical cystectomy will be performed to evaluate the possible relationship between technical and nontechnical skills. Radical cystectomy was chosen for this analysis because it is a lengthy, complex, and demanding surgery for the surgeon and other team members.

Since radical cystectomy surgeries take many hours to complete, a long-term and detailed analysis is possible per procedure. Radical cystectomy is traditionally performed using an open surgical approach (open radical cystectomy) at the Catharina Hospital Eindhoven, but recently a shift is made to robot-assisted radical cystectomy. This shift enables us to investigate in which manner nontechnical skills change during the introduction of robot-assisted radical cystectomy. The nontechnical skills during the learning curve of robot-assisted radical cystectomy in the Catharina Hospital Eindhoven will be compared with the nontechnical skills during the open radical cystectomy in the same hospital as well the nontechnical skills of an experienced robot-assisted radical cystectomy team in the Antoni van Leeuwenhoek Hospital.

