## Design

The present study is a prospective, observational, multicentre, nonrandomised, case-control study that will include all patients undergoing either an open radical cystectomy or a robot-assisted radical cystectomy in Catharina Hospital Eindhoven or Antoni van Leeuwenhoek Hospital.

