### Inclusion criteria

Patients who will undergo either an open radical cystectomy or a robot-assisted radical cystectomy in Catharina Hospital Eindhoven or Antoni van Leeuwenhoek Hospital are eligible for this study. The choice of treatment is at the discretion of the patient and the surgeon.

For study inclusion, the following criteria must be met:1.Patients must be aged ≥18 yr.2.Patients must be able to understand and sign an informed consent form.3.Patients will undergo either an open radical cystectomy or a robot-assisted radical cystectomy in Catharina Hospital Eindhoven or Antoni van Leeuwenhoek hospital.4.Indication for the radical cystectomy must be urothelial cell carcinoma of the bladder.5.Informed consent of the patient must be obtained to gather data and perform observations during surgery.

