## Statistical analysis

Frequency statistics will be calculated for patient demographical data, and a Shapiro-Wilk test with *p* > 0.05 will be used to define normal distribution. Univariate analysis will be conducted to test for statistically significant differences in observation scores between open radical cystectomy and robot-assisted radical cystectomy cohorts across all variables, using independent sample *t* tests and Mann-Whitney *U* testing, as appropriate. A variable-selection strategy will be used to create multivariate models. Binary logistic regression will be conducted to calculate odds ratios and 95% confidence intervals for significant predictors on univariate analysis and clinically relevant covariates. Statistical significance is set at *p* < 0.05 based on a two-tailed comparison. Statistical analyses will be performed using SPSS Statistics version 24 (IBM, Armonk, New York, USA).

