### Secondary outcome measurements

Age, World Health Organization performance status, Charlson comorbidity index, neoadjuvant chemotherapy, prior local treatment, prior radiation therapy in the surgical field, diagnosis, prior abdominal and/or pelvic surgery, indication of surgery, perioperative complications, postoperative complications according to the Clavien-Dindo system [24], length of hospital stay, stay in the intensive care unit, blood loss, patient-reported experience measures, patient-reported outcome measures, method of surgery, and oncological outcome (surgical margins and number of resected lymph nodes, and pathology results) will be registered prospectively. Patient follow-up will be for at least 30 d. Surgeon-specific data will be recorded (ie, age, gender, right or left handedness, gaming experience, and prior surgical and robot-assisted surgery experience of the surgeon).

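### Univariate p < 0.05 is a route into the logistic models of a self-selected comparison, and nothing commits the plan to keeping surgical approach in them

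*Protocol article*

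**What the plan says.** The Statistical analysis section of the protocol article sets out three steps. The first is univariate: "Univariate analysis will be conducted to test for statistically significant differences in observation scores between open radical cystectomy and robot-assisted radical cystectomy cohorts". The second is model building: "A variable-selection strategy will be used to create multivariate models". The third is the entry rule: "Binary logistic regression will be conducted to calculate odds ratios and 95% confidence intervals for significant predictors on univariate analysis and clinically relevant covariates". The only threshold given is the general one: "Statistical significance is set at *p* < 0.05 based on a two-tailed comparison".

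Four other places bear on this rule:
- **Design** calls the study a "prospective, observational, multicentre, nonrandomised, case-control study that will include all patients".
- **Inclusion criteria** says how approach is assigned: "The choice of treatment is at the discretion of the patient and the surgeon".
- **Introduction and hypotheses** states the aim of finding how the robot "influences both nontechnical skills and surgical outcomes during the 1st year of robot-assisted radical cystectomy compared with open radical cystectomy".
- **Secondary outcome measurements** lists the patient characteristics, including "Charlson comorbidity index, neoadjuvant chemotherapy, prior local treatment, prior radiation therapy in the surgical field", in one list with method of surgery, complications and surgical margins. Exposure, potential confounders and outcomes are not separated.

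**The concern.** When patient and surgeon choose the approach, the crude association between approach and a surgical outcome is the confounded quantity. Adjustment exists to correct it. A rule that consults the crude p value before deciding whether to estimate the adjusted effect works in the wrong order.

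If the patients who receive one approach differ in risk in a way that offsets a real difference, the crude test tends to miss it. Approach can then be removed before adjustment could reveal the difference. The same can happen to a confounder that fails its own univariate test and is not judged clinically relevant.

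At stake is the surgical-outcome part of the aim. The three hypotheses and the primary outcomes concern skills and are not the target of this point.

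**Working it through.** The protocol article gives no sample size, event rate or power for this analysis, so there is no figure of its own to reproduce. The check has three parts.

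**1. Largest plausible size.** Centre details gives 35 cystectomies a year in the first hospital and 50 + 50 = 100 in the second, together 135. Time scales gives January 2021 to August 2022, about 19 to 20 months.
- 135 × 19/12 = 213.75
- 135 × 20/12 = 225

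The ceiling is therefore about 214 to 225 procedures, before any loss for consent, withdrawal or indication. The simulation uses 2 × 112 = 224.

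**2. How masking arises.** All inputs here are assumptions. The complication risk is 25% in open patients without the risk factor, so the odds are 1/3. The risk factor has odds ratio 2.5 and the true robot odds ratio is 2.0. The cell risks are:
- open, no factor: 0.250
- open, factor: odds 0.833, risk 0.455
- robot, no factor: odds 0.667, risk 0.400
- robot, factor: odds 1.667, risk 0.625

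Let the factor be present in 25% of robot and 50% of open patients.
- Robot risk = 0.75 × 0.400 + 0.25 × 0.625 = 0.456
- Open risk = 0.50 × 0.250 + 0.50 × 0.455 = 0.352
- Crude odds ratio = (0.456/0.544) / (0.352/0.648) ≈ 1.54, against a true 2.0
- Standard error of the risk difference = √(0.456 × 0.544/112 + 0.352 × 0.648/112) ≈ 0.065
- z = 0.104/0.065 ≈ 1.6, so the chance of crude p < 0.05 is about Φ(1.6 − 1.96) = Φ(−0.36) ≈ 36%

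**3. Simulation.** The univariate screen at two-sided p < 0.05 is compared with a logistic model that always contains approach and the risk factor. The last column counts trials in which approach fails the screen although its adjusted effect is significant.

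| Factor present, robot vs open | Passes screen | Significant in forced model | Significant effect screened out |
|---|---|---|---|
| 25% vs 50% (strong masking) | 35% | 66% | 31% |
| 35% vs 45% (mild masking) | 53% | 68% | 14% |
| equal (no selection) | 67% | 70% | about 4% |
| reversed (higher-risk patients to robot) | – | – | 0% |

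The 35% in the first row agrees with the hand calculation.

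A second set of assumptions gives the same picture: N = 225, baseline risk about 35%, a factor with prevalence 50% and odds ratio 3, and a protective robot odds ratio of 0.5. Here masking needs higher-risk patients to go to the robot.
- No selection: approach passes the screen in 61% and is significant in the forced model in 62%.
- 65% of high-risk against 35% of low-risk patients get the robot: 20% against 58%.
- 75% against 25%: 6% against 51%.

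**The case against.** The strongest reply is that the quoted sentence has two routes into the model, and the second, clinical relevance, has no p-value condition. This stands for case-mix. Age, performance status, the Charlson index and prior radiation are obvious candidates. A reader might infer that univariate significance alone decides what enters and that every case-mix variable must pass it; the sentence does not support that.

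It stands only in part for approach. Nothing forbids admitting approach as clinically relevant, and method of surgery sits in the same list as the patient characteristics. So a reader might infer that a masked robot effect is bound to be dropped, but it only can be. Equally, nothing says that approach is exempt from the screen, and the decision is left open until the data are seen.

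Second, the dependent variable of the logistic regression is not named, and the only univariate tests described compare observation scores. That the models concern surgical outcomes is an inference. It is a reasonable one, since complications and margins are natural binary outcomes on record, but it remains an inference.

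Third, an unnamed selection strategy or missing covariate list may be settled in a fuller document that is not shown. Those gaps are not the point. The point is the entry rule that the article does state.

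Two further inferences from the simulation should be resisted:
- **Excess false positives.** With no true effect and strong selection, approach passes the screen in about 12 to 14% of trials, against about 5% significant in the forced model. Passing the screen only admits approach to the adjusted model. About 2.6% both pass and stay significant after adjustment, so no excess is shown.
- **Exaggerated odds ratios.** When approach survives the screen under strong masking, the mean adjusted odds ratio is 2.7 against a true 2.0. The forced model, restricted to its own significant results, already averages 2.4, so more than half of the inflation is ordinary selection on significance.

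**Conclusion.** The point holds in limited form. The plan states univariate significance as an entry criterion in a comparison where approach is self-selected, and it does not commit to keeping the exposure in the model. A confounded crude p value can therefore remove approach, or a confounder not judged clinically relevant, before adjustment.

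Under the assumed inputs, the loss of a significant adjusted effect runs from 0% to about 31%. It rests on the assumed effect, the strength of the risk factor, full accrual at centre volume, and above all the direction and strength of selection, which the documents do not give. With no selection the loss is small. The concern falls on secondary outcomes, but these belong to the stated aim and the correction is inexpensive, so the change should be made.

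**What to change.** Where the logistic models address surgical outcomes such as complications or margins, remove univariate significance as an entry criterion. State that each such model always contains:
- surgical approach;
- hospital;
- a short fixed set of recorded confounders: age, WHO performance status, Charlson index, prior abdominal or pelvic surgery, prior radiation and neoadjuvant chemotherapy.

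Specify a penalised fit (Firth or ridge) if events are few. Move these variables out of the secondary outcome list into a covariate list, and name method of surgery as the exposure.

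The cost is wording and a few degrees of freedom; every variable is already collected.

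One limit remains. Under Study population, one surgeon performs all open and another all robot-assisted procedures in the first hospital, while a single surgeon performs both in the second. In the first hospital approach cannot be separated from surgeon by any adjustment, and the adjusted odds ratio should be interpreted with that stated.

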### Primary outcome measurements

The following outcomes will be reported.

Nontechnical skills will be observed using five different methods:1.NOTSS [16]: The focus of the NOTSS assessment method lies on the following aspects of nontechnical skills:(a)Situation awareness: developing and maintaining dynamic awareness of the situation in operating theatre based on assembling of data from the environment, understanding of what they mean, and thinking ahead about what may happen next.(b)Decision making: skills for diagnosing the situation and reaching a conclusion in order to choose an appropriate course of action.(c)Communication and teamwork: skills for working in a team context to ensure that the team has an acceptable shared overview of the situation and can complete tasks effectively.(d)Leadership: leading the team and providing direction, demonstrating high standards of clinical practice and care, and being considerate about the needs of individual team members.2.Oxford NOTECHS II [11], [12]: The focus of the NOTECHS II assessment method lies on the following aspects of nontechnical skills:(a)Leadership and management.(b)Teamwork and cooperation.(c)Problem solving and decision making.(d)Situation awareness.3.OTAS [21]: ^The^
^focus^
^of^
^the^
^OTAS^
^assessment^
^method^
^lies^
^on^
^the^
^following^
^aspects^
^of^
^nontechnical^
^skills:^(a)Communication.(b)Coordination.(c)Cooperation and back-up behaviour.(d)Leadership.(e)Team monitoring and situational awareness.4.ICARS [17]: The focus of the ICARS assessment method lies on the following aspects of nontechnical skills:(a)Checklist and equipment.(b)Interpersonal skills (communication and team skills, and leadership).(c)Cognitive skills (decision making and situational awareness).(d)Resource skills (stress and distractors).(e)Human factor analysis [22]: Human factor analysis consists of four levels of system failure: unsafe acts, preconditions for unsafe acts, unsafe supervision, and organisational influences.5.Perioperative events (ie, people entering or leaving the OR, phone calls, etc.).

Technical skills in robot-assisted radical cystectomy will be analysed using two different methods:1.GEARS [7]: The focus of the GEARS assessment method lies on general robot surgical principals, that is, depth perception, bimanual dexterity, efficiency, force sensitivity, autonomy, and robotic control.2.GERT [5]: The focus of the GERT assessment method lies on the capture and analysis of technical errors and resulting events during laparoscopic procedures.

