### Measurements

Nontechnical skills will be observed using five different methods:1.NOTSS: Nontechnical Skills for Surgeons [16].2.Oxford NOTECHS II: a modified theatre team nontechnical skills scoring system [11], [12].3.OTAS: Observational Teamwork Assessment for Surgery [21].4.ICARS: evaluation of nontechnical skills in robotic surgery [17].5.Analysis of human factors [22].

No intracorporeal videos of open radical cystectomy can be recorded due to blocking of the image by the surgeons and the OR lights, and difficulty getting a clear view into the surgical area in the pelvic region from a distance. The analysis of technical skills will be performed only using the robot-assisted radical prostatectomy videos. This method of analysis will be performed to investigate the influence of robot-assisted surgery experience on nontechnical skills and outcome of the surgery. Technical skills in robot-assisted radical cystectomy will be analysed using two different methods:1.GEARS: Global Evaluative Assessment of Robotic Skill [7].2.GERT: Generic Error Rating Tool [5].

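### All tools are primary outcomes with no lead score and every comparison is tested at two-sided 0.05, so the chance of at least one false positive is well above 5%

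*Protocol article*

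**What the plan says.** **Primary outcome measurements.** The list gives NOTSS with four aspects, Oxford NOTECHS II with four, OTAS with five and ICARS with four. Human factors follow as "Human factor analysis [22]: Human factor analysis consists of four levels of system failure", printed as item (e) under ICARS. The fifth numbered item is "Perioperative events (ie, people entering or leaving the OR, phone calls, etc". GEARS and GERT come next under the same heading, before the secondary outcomes begin. No score is singled out or ordered.

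**Statistical analysis.** The univariate tests look for "differences in observation scores between open radical cystectomy and robot-assisted radical cystectomy cohorts across all variables". The threshold is given once: "Statistical significance is set at *p* < 0.05 based on a two-tailed comparison". The regression then takes up "significant predictors on univariate analysis and clinically relevant covariates".

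**Measurements** (abstract and Protocol overview). Human factors are the fifth method here, and perioperative events are not listed. ICARS appears as "ICARS: evaluation of nontechnical skills in robotic surgery". The Protocol overview explains that open cases give no usable intracorporeal video, and continues: "The analysis of technical skills will be performed only using the robot-assisted radical prostatectomy videos".

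**Introduction and hypotheses.** Robot cases in Eindhoven are to be compared with open cases there and with the experienced robot team in Amsterdam. Hypothesis 2 adds experienced robot teams against experienced open teams. No hypothesis names a tool or a score.

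**The concern.** A set of equal primary outcomes, each tested at 0.05, does not hold the overall error at 5%. The hypotheses name no score, so a significant difference on any tool could be put forward as support. Hypothesis 3, on different forms of behaviour, could be claimed from any domain in either direction. The same univariate p-values also decide what enters the regression, so a chance finding can be carried forward into the models.

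Two features make the primary set harder to pin down. The two lists of five methods differ in their fifth entry. The set also includes tools that the stated open-versus-robot comparison cannot use (GEARS, GERT) or may not be able to use (ICARS).

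**Working it through.** The article states no overall error rate, sample size or power, so there is no figure of its own to reproduce. The check counts the tests and computes the chance of at least one false positive when no true difference exists.

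**Counts, from Primary outcome measurements**
- One total per method, for the five methods under Measurements: 5.
- NOTSS, NOTECHS II and OTAS by domain: 4 + 4 + 5 = 13.
- Adding four human-factor levels, and perioperative events as one outcome: 13 + 4 + 1 = 18.
- Adding four ICARS domains, if ICARS is scored in open cases: 18 + 4 = 22.
- GEARS and GERT are excluded, as they have no open comparator.

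**One open-versus-robot contrast.** For m independent tests the chance is 1 − 0.95^m. For 13 this is 1 − 0.95^13 = 48.7%, and for 22 it is 1 − 0.95^22 = 67.6%. For correlated scores, m standard normal statistics with common correlation ρ were simulated (200,000 replicates), counting any |z| above 1.96. The values of ρ are assumptions.

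| Tests | Independent | ρ = 0.3 | ρ = 0.5 | ρ = 0.7 | ρ = 0.9 |
|---|---|---|---|---|---|
| 5 | 22.6% | 20.8% | 18.3% | 14.9% | 10.1% |
| 13 | 48.7% | 41.9% | 33.4% | 23.9% | 13.8% |
| 18 | 60.3% | 50.9% | 39.7% | 27.7% | 15.2% |
| 22 | 67.6% | 56.8% | 44.0% | 30.2% | 15.9% |

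The expected number of false positives is 0.05 × m: 0.25, 0.65, 0.90 and 1.10.

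**Three contrasts.** These are Eindhoven robot v Eindhoven open, Eindhoven robot v Amsterdam robot, and Amsterdam robot v Amsterdam open. The last is taken as the reading of hypothesis 2. Group sizes follow from Time scales (20 months) and Centre details, assuming that every patient consents: 35 × 20/12 ÷ 2 ≈ 29 per approach in Eindhoven and 50 × 20/12 ≈ 83 in Amsterdam. Shared groups were kept in the simulation (40,000 replicates).

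| Scores | Independent | ρ = 0.5 | ρ = 0.7 | ρ = 0.9 |
|---|---|---|---|---|
| 5 | 49.7% | 42.1% | 34.8% | 24.5% |
| 13 | 83.5% | 66.3% | 51.9% | 32.7% |
| 22 | 95.4% | 78.9% | 61.5% | 36.4% |

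**The case against.** **Multiplicity is usually left to the analysis plan.** This is true, and the absence of an adjustment from a condensed article would not be a finding by itself. But this article does fix something: it designates the whole list as primary and sets one threshold for all variables. An unseen plan could add an adjustment, but it could not make one score primary without departing from the printed list.

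**The domains overlap.** Situation awareness and leadership recur across the behavioural tools, and the same two observers score the same videos. Independence is therefore implausible. This stands, and it is why the result is given as a range.

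**Domain-level testing is a reading.** The article does not say whether domains or totals are tested. This also stands, so five totals form the lower case. Nor can the number of event outcomes be counted, as the article gives only examples.

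**Stronger readings that the documents do not support**
- A reader might infer that a false positive is likely. For one contrast the chance stays below one half at ρ of 0.5 or more, for every count considered.
- A reader might infer that a false positive could not be recognised. The article undertakes to report the listed outcomes, so readers could count and adjust the tests. What they would lack is a result named in advance as the confirmatory one.
- A reader might infer that GEARS and GERT add to the open-versus-robot error. They cannot, because technical skills are analysed on robot videos only.
- A reader might infer that scoring ICARS in open cases biases the comparison in a known direction. The article neither says that ICARS is used there nor shows items that would not apply.
- The two lists might be read as rival sets of methods. The placing of human factors under ICARS is probably a numbering slip, and no method is lost between them. What remains is that perioperative events are primary in one place and absent from the other list.

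**Conclusion.** The point holds in a limited form. Following the stated rule, one open-versus-robot contrast carries an overall false-positive risk of about 10–23% with five totals and 14–68% with 13 to 22 domains, against a nominal 5%. Over three contrasts it is about 25–50% and 33–95% respectively. The ends of each range are a correlation of 0.9 and independence. The figures assume no true difference anywhere, equal correlation between scores, and single tests that each hold their own 5% level. Even the most favourable case is about twice nominal. The defect is the lack of a prespecified lead result. It should be corrected, but it does not show that any particular finding will be false. The reference to prostatectomy videos is an editorial slip: the study covers cystectomy only, and the same section says so.

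**What to change.** 1. Name one primary score that can be applied to both approaches, and one primary contrast, tested at two-sided 0.05. The choice of score is the sponsor's. The article describes no total for any tool, so the score chosen must be defined.
2. Make all other scores and contrasts secondary with Holm or false-discovery control, or label them exploratory.
3. State that GEARS and GERT enter only robot-versus-robot and learning-curve analyses. State whether ICARS is scored in open cases and enters the open-versus-robot comparison.
4. Reconcile the Measurements lists with Primary outcome measurements on whether human factors and perioperative events are both primary.
5. Correct prostatectomy to cystectomy under Measurements (editorial).

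**Cost.** The text changes are small and the primary test keeps its full 0.05. The price is lower power for the other scores. With Bonferroni as the strict case, an assumed standardised difference of 0.5 and a normal approximation:

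| Per approach | 0.05 | 0.05/5 | 0.05/13 | 0.05/22 |
|---|---|---|---|---|
| 29 (Eindhoven) | 48% | 25% | 16% | 13% |
| 29 + 83 = 112 (both sites) | 96% | 88% | 80% | 76% |

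Holm would lose somewhat less. If that loss is unacceptable for the Eindhoven-only comparison, the exploratory label is the honest alternative.
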